# AIM OF STUDY / RESEARCH QUESTION

The objective of this study is to assess the feasibility and efficacy of a using a myofunctional device to improve oral care and swallowing function in an aged care population.

# STUDY DESIGN/METHODOLOGY

The protocol presented is based on both the Standard Protocol Items: Recommendations For Interventional Trials (SPIRIT) (2013) and Consolidated Standards of Reporting Trials (CONSORT) (2018) guidelines, to conduct an acceptability and feasibility pilot study. The proposed protocol is for a new intervention. There have been no previous trials using the MyoMunchee
[figure not shown]
 (a myofunctional device) in the area of oral hygiene and dysphagia with those in an aged care setting. A cluster randomised control trial in Sweden by Hagglund and colleagues (2019) utilised a myofunctional device (used for promoting lip closure and nasal breathing) for oral neuromuscular training for those 65 years and older in short term care units with impaired swallowing. Hagglund and colleagues (2019) study indicated that swallowing function significantly improved for those in the intervention group immediately following 5 weeks of therapy with the use of the myofunctional device, and a significant reduction in signs of aspiration compared to the control group 6 months post treatment.

The use of this study will provide important information regarding the feasibility and efficacy of a new treatment for oral hygiene and dysphagia with the MyoMunchee
[figure not shown]
, and provide information for calculating the sample size needed for a randomised control trial (In, 2017, & Eldridge, et al., 2016). Thabane and Lancaster (2019), In (2017), and Eldridge, et al., (2016) highlight the importance of feasibility studies to further guide and inform conduct and design of a larger clinical trial or future research.

The feasibility of the treatment intervention will be measured by way of:

- Verbal survey of the residents receiving the intervention regarding experience using the device, using a 5-point Likert scale (very difficult – very easy), and dichotomous questions (yes – no) (Appendix A).
- Questionnaire for care staff (nursing/allied health) in the implementation and acceptability of assisting participants with the myofunctional device, using both a 5-point Likert scale (very difficult – very easy), dichotomous questions (yes – no), and free text (Appendix B).
- The consenting rates,
- Treatment completion rates,
- Treatment adherence (which will be monitored on the daily check list provided by care staff, see Appendix C, D, E, F, G).

Efficacy will be measured through the collection of pre and post intervention outcome measures using validated instruments to measure perceived dysphagia symptoms, and the presence of dysphagia. These outcome measures include:

- Oral Health Assessment Tool (OHAT) (Chalmers, Johnson, Tang, Titler, 2004) (Appendix H)
- Timed Water Swallowing Test (TWST) (Hughes &Wiles, 1996) (Appendix I)
- Test of Mastication and Swallowing Solids (TOMASS) (Huckabee, et al., 2018) (Appendix J)
- Mann Assessment of Swallowing Ability (MASA) (Mann, 2002) (Appendix K)
- Eating Assessment Tool (EAT-10) (Belafsky, et al., 2008) (Appendix L)
- Mini Mental State Examination (MMSE) (Malloy & Clarnette, 1999) (Appendix M)
- Functional Oral Intake Scale (FOIS) (Cary, Mann, & Groher, 2005) (Appendix N)

# STUDY SETTING/LOCATION

This will be a single intervention site study, conducted at Maroba Aged Care, Newcastle, Australia, with data analysis occurring at the University of Newcastle, Australia.

1. **Sites**

This study will involve recruitment of residents and care staff from Maroba Aged Care and will be conducted by researchers from the University of Newcastle, with the assistance of care staff (nursing/allied health) at Maroba Aged Care. Data once collected will be stored on a secured drive at the University of Newcastle for analysis.

# STUDY POPULATION AND SETTING

Eligible residents at Maroba Aged Care who meet the selection criteria outlined below and who consent to participating in the study will receive intervention.

Care staff (nursing/allied health) who consent to participate in the study will be responsible for overseeing the intervention of residents who are consented to the study.

# ELIGIBILITY CRITERIA

Residents:

**Inclusion criteria**

1. age > 65 years

2. Ability to understand English and follow instructions for timed water swallow test and use of the myofunctional device

3. Residents receiving texture modified diets and/or fluids

4. Residents with natural teeth, dentures (partial and full), and edentulous

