# STUDY OUTCOMES

1. **Quantitative**
2. **Primary Outcome**

Feasibility and acceptability of treatment intervention. This will include the number of participants approached versus consented, completed treatment rates, and adherence to the intervention (monitored by care staff with supervision of the intervention, and completion of daily intervention sheets).

1. **Secondary Outcome(s)**

Secondary outcome measures will be collected both pre and post intervention, and are outlined in Table 1.

**Table 1** Secondary outcome measures for collection pre and post intervention

| Outcome Measure | Reference | Outcome | Description |
| --- | --- | --- | --- |
| Oral Health Assessment Tool (OHAT) | [6] | Oral health | Reliable and valid screening tool for use in aged care and with cognitive impairment; Approximately 7-8 minutes to administer; 8 items, Rating scale – 0 = healthy, 1 = changes, 2 = unhealthy; Total score out of 16, The higher the score the worse the oral health; Items that score 1 indicate intervention is required, and items scoring 2 indicate referral to a dental professional is required |
| Timed Water Swallow Test (WST) | [18] | Aspiration risk | Swallow speed is a sensitive indicator for identifying patients at risk of swallow dysfunction; Choking in 100ml WST may be a potential indicator for follow up aspiration; Measures swallow time, number of swallows and observes for signs of choking; Abnormal swallow is defined as a speed below 10ml/s (amount of water divided by elapsed time); Count the number of swallows taken to consume 100mls water; Time taken to consume 100mls water |
| Test of Mastication and Swallowing Solids (TOMASS) | [17] | Mastication ability | Quantitative assessment of solid bolus ingestion; Sensitive in detecting changes in performance ability of mastication; High interrater and test-retest reliability; Count number of bites, number of masticatory cycles per bite, number of swallows per bite; More likely to identify patients with subtle oral phase impairment or bolus transition issues; Normative ranges in older adults: number of bites (male 1.47/female 1.87), time in seconds (male 32.61/female 41.85), total number of swallows (male 3.61/female 3.5), masticatory cycle (male 37.6/female 41.65) |

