# STUDY PROCEDURES

1. **Recruitment of participants**

All residents and care staff who meet the selection criteria will be eligible to participate in this study. They will be identified by the Nursing Unit Managers (NUM) and the speech pathologist/s at Maroba Aged Care and provided with an information flyer (Resident Information Flyer, Appendix O. Care Staff Information Flyer, Appendix P). The residents/families of residents/care staff will be provided with a participant information statement (Residents, Appendix Q. Care staff, Appendix R) regarding the study, and then followed up by the NUM/speech pathologist for interest in study participation. There will be an opportunity for residents, family of residents, and care staff to ask questions before and after consenting to participation. Questions regarding the study can be directed by the staff at Maroba Aged care to the Principal Investigator. Residents/family of residents/care staff will be required to sign and provide written consent for participation (Residents, Appendix S. Care staff, Appendix T). Consideration and return of consent for participation in the study will be 7 days after initial contact.

Explanation will be provided to residents/family of residents that their usual oral health care and dysphagia treatment will not vary with or without participation in this study. Further to this, a statement will be provided to participants that based on the results of the pilot study, the larger clinical trial may not be performed.

This research will involve the use of information without personal identifiers and it will be obtained from individuals or gathered from medical files by care staff appointed by Maroba Aged Care. The existing data information seen in section 9d. will be collected for each consented resident.

As this is a feasibility study utilising a myofunctional device not previously trialled in this setting, all consented residents will receive the treatment intervention to better understand acceptability of the device and feasibility of completing a larger trial. No randomisation of participants will occur. The number of participants that will be aimed for recruitment – up to 50 residents and 10 staff. This is based on the available recruitment pool, and the number of residents who may not give consent. Because this is a feasibility study this does not require sample size base.

The period of time for expected time to recruit participants is four weeks.

1. **Study procedures**

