Staff:

Education will be provided before the commencement of the trial intervention by the principal investigator from the University of Newcastle to care staff, regarding familiarization and instructions for use of the myofunctional device (MyoMunchee
[figure not shown]
), cleaning and storage of the device, and documentation of device use.

The use of a myofunctional device (MyoMunchee
[figure not shown]
) will be required for each participant for the duration of this intervention and will be provided in kind by MyoMunchee
[figure not shown]
. Further explanation regarding the cleaning, cleaning schedule and storage of this will be provided in the treatment protocol as per MyoMunchee
[figure not shown]
 cleaning protocol.

The research team will provide the residents/care staff with instructions and a guide for the use of the device. This will require active use of the device with the action of chewing.

The use of the myofunctional device will be monitored by the care staff at Maroba Aged Care, with documentation on a daily checklist provided for each participant. The daily checklist will be collected by the care staff at Maroba Aged Care at the end of each week of intervention and entered into an electronic database each week by the principal investigator.

Following the five week intervention, the care staff will be asked to complete a questionnaire regarding acceptability and feasibility of the trial intervention.

Residents:

Once participants who meet the selection criteria are enrolled in the study, outcome measures will be collected and stored by the principal investigator from the University of Newcastle. The collection of outcome measure should take approximately 60 minutes for each participant.

There will not be any alteration to the participant’s usual intervention for oral care or swallowing treatment unless this is deemed appropriate by the usual treating speech pathologist/s at Maroba Aged Care, or the treating medical/nursing team.

The trial intervention using the myofunctional device will commence within two weeks post pre-treatment outcome measure collection.

The myofunctional device (MyoMunchee
[figure not shown]

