| **Underlying Medical Diagnosis** | - CVA– year _________________ - Dementia - Parkinson’s Disease - Cardiovascular disease - Cancer – specify _____________ - COPD - Diabetes - Multiple Sclerosis - Epilepsy | | | - Hypertension - Osteoporosis - Arthritis - Depression - Asthma - Motor Neuron Disorder - Polymyositis - Other_______________________   ___________________________ | |
| **Dentition (own, edentulous, dentures)** | Own/Dentures/Edentulous | | | | |
| **Diet/Fluid consistency** | - NBM - PEG - JJ Tube - Other _________ | - Liquidized - Puree - Minced Moist - Soft Bite Sized - Easy Chew - Normal Diet | | | - Extremely Thick - Moderately Thick - Mildly Thick - Slightly Thick - Thin fluids |
| **MMSE score/date last assessment** | Score: | | Date: | | |
| **Independence in oral care** | Yes/no/maybe/unsure | | | | |
| **Living status** | Independent living/ACF (check terminology) | | | | |

1. **Safety considerations**

This study involves a new intervention with a vulnerable population. However, the intervention uses a device that has Therapeutic Goods Approval and the residents who will be using this device will be monitored by care staff during the intervention.

Potential Risks and Solutions for residents undertaking intervention

| **Potential Risks** | **Solutions** |
| --- | --- |
| Aspiration of saliva secondary to increased saliva production during device use | Aspiration of saliva occurs daily. The continued use of usual oral care during this study to ensure adequate oral hygiene should assist with reducing complications that may arise from aspiration of saliva  Monitoring by care staff to ensure participants have adequate salvia management/control  If coughing occurs through use of the device and increased saliva production, a referral will be made for speech pathology at Maroba to review swallowing function (and appropriateness for continuation in study) |
| Initial discomfort to gums/jaw with the action of chewing the device | The treatment intervention has been staged in time use of the device, increasing weekly to allow for adjustment to oral comfort. If oral discomfort is identified/reported, a review by the researcher and speech pathologist at Maroba Aged care will take place and recommendations will be made for continuation in the study.  Sizing and selection of the device has been considered for oral comfort and ease placing and removing the device from the oral cavity with an eternal tab/handle. |

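### Harm from the study's own swallow tests falls outside the risk table and the adverse event definition, and the text shown does not tie those tests to a resident's prescribed texture

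*Protocol*

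**What the plan says.** **Who enters.** Resident inclusion criterion 3 admits "Residents receiving texture modified diets and/or fluids" and sets no level. The data form under Access to Existing Data provides for the full fluid range, "Extremely Thick - Moderately Thick - Mildly Thick - Slightly Thick - Thin fluids", and for diets down to puree and liquidised. The recruitment target is "up to 50 residents and 10 staff".

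**What they are asked to do.** STUDY OUTCOMES, Table 1, lists the timed water swallow test on 100 ml of water and TOMASS, both before and after the intervention, for no named subset. Of the water test it says: "Choking in 100ml WST may be a potential indicator for follow up aspiration". It describes TOMASS as "Quantitative assessment of solid bolus ingestion".

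**When.** Device use "will commence within two weeks post pre-treatment outcome measure collection", so the first round of tests precedes any exposure to the device.

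**Safety provisions.** The risk table under Safety considerations has three rows: saliva aspiration while the device is in use, gum or jaw discomfort from chewing it, and infection control. Coughing with the device leads to a speech pathology referral. Under Unexpected or Serious Adverse Events, an adverse event (AE) is limited to harm that the intervention causes, and the study procedures are described as carrying no more than minimal risk.

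**Usual care.** Residents are told that "usual oral health care and dysphagia treatment will not vary with or without participation in this study". The resident procedures also rule out altering a participant's "usual intervention for oral care or swallowing treatment unless this is deemed appropriate" by the treating speech pathologist or the medical or nursing team.

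**The concern.** The inclusion criterion selects residents because their food or drink has been modified, usually a sign that an ordinary consistency is thought difficult or unsafe for them. The two tests use thin water and a solid. For a resident whose prescription bears on one of them, that test is the part of the study most likely to provoke coughing or choking, and Table 1 itself names choking for the water test. Yet the written safety provisions are built around the device.

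At stake is whether a non-serious event during a test has a planned response, is recorded as an AE and is counted in the safety results. A feasibility study meant to inform a larger trial should be able to report how well its assessments were tolerated.

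**Working it through.** The point rests mainly on setting the provisions side by side; the arithmetic only sizes the exposure. The Protocol has no figure of its own to reproduce.

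**1. Is either test tied to prescribed texture in the text shown?**
- Inclusion 2 requires the resident to follow the water test instructions. That screens comprehension, not safety on thin fluid.
- Inclusion 3 sets no level.
- None of the five resident exclusions mentions texture. Exclusion 3 concerns ability to comply, with a behavioural example.
- Table 1 attaches no condition to either test.

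So there is no link in the body of the Protocol. Appendices I and J could supply one.

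**2. Does the risk table cover the tests?** Three of three rows concern the device or its cleaning; none concerns the water test or TOMASS. The only stated response to coughing is for coughing with the device.

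**3. How would a non-serious choking event at a baseline test be classified?**
- *AE:* the intervention must have caused it. The device has not yet been used, so this fails.
- *Serious adverse event (SAE):* death, threat to life, hospitalisation or significant disruption of function. A non-serious event fails by construction.
- *Unexpected event (UE):* the incident must warrant considering a change to the intervention protocol for the participant's safety. A test event might meet this but need not.

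The event is thus captured only if someone judges it a UE. At the post-treatment tests the device has been used, so causation could be argued, but an event provoked by the water or the solid is still not obviously caused by the intervention.

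**4. Exposure.** Inputs: 50 residents at most (recruitment target), 2 tests and 2 visits (Table 1).
- All administrations: 50 × 2 × 2 = 200.
- At baseline: 50 × 2 = 100.

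These are ceilings. They include residents whose prescription permits both tests, because the AE definition applies to everyone.

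**5. The subset for whom texture matters.** The Protocol does not give the share f whose prescription rules out a given test. Over an assumed range:

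| f | Residents (50 × f) | Administrations of that test (× 2 visits) | Of these at baseline | Pairs left if not tested |
|---|---|---|---|---|
| 10% | 5 | 10 | 5 | 45 |
| 20% | 10 | 20 | 10 | 40 |
| 40% | 20 | 40 | 20 | 30 |
| 60% | 30 | 60 | 30 | 20 |

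No choking rate per test is given, so no expected number of events is computed.

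**The case against.** The strongest reply is that the tests have their own appendices, I and J, which are the natural place for who may be tested and when to stop, and they are not shown. The usual-care statements also matter: a prescribed texture can fairly be read as part of dysphagia treatment, so testing against it without the treating team's agreement would depart from the Protocol. The facility's speech pathologists help to identify eligible residents, and a speech pathologist with more than 17 years of clinical experience does the testing.

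A reader might infer from inclusion 3 and Table 1 that the plan has residents given thin water or solids against their prescription. The documents do not support that, for the reasons just given. They show only that the body of the Protocol does not state the condition.

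Exclusion 3 is sometimes read as the missing exemption, since it mentions ability to comply with all procedures. It does not name texture, and if stretched that far it would remove many of the residents whom inclusion 3 seeks.

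On safety capture, the reply is partly right. The SAE and UE definitions are not expressly confined to the device, all three classes of event are assessed for severity, and a participant can be discontinued for a medical condition as well as for an AE. What remains is the non-serious test event that nobody classes as a UE. The unseen appendices would not close that gap, because the risk table and the AE definition are in the text shown.

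**Conclusion.** The concern holds in a limited form and is worth fixing before enrolment. The firm part is that the risk table omits both swallow tests and that the AE definition leaves out a non-serious choking or aspiration event in a test, most clearly at baseline. This applies to up to 200 administrations, up to 100 of them before the device starts. The conditional part is that nothing in the text shown ties either test to prescribed texture; Appendices I and J may do so. The 10% to 60% range for residents affected is an assumption.

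A reader might also infer biased water test or TOMASS results. The documents do not support that: direction and size would depend on who is left untested, which is not stated. No bias and no event rate are claimed, and the primary feasibility outcome is not affected.

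**What to change.** 1. Define AEs as untoward medical occurrences during, or resulting from, the intervention or any study assessment.
2. Add the water test and TOMASS to the risk table, with a response to coughing or choking modelled on the existing one for the device: stop the test and refer to speech pathology.
3. State in the body of the Protocol that each test is given only if the resident's prescribed texture permits it or the treating speech pathologist clears it. If Appendix I or J already says this, a cross-reference is enough.

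The drafting cost is a few words, two table rows and one sentence. The cost in data is fewer residents on two secondary outcomes. With 50 enrolled and no dropout, the 95% confidence interval half-width for the mean paired change, in SDs of the differences, is t(0.975, n − 1)/√n:
- n = 50: 2.010/7.071 = 0.28
- n = 45 (10% untested): 2.015/6.708 = 0.30
- n = 20 (60% untested): 2.093/4.472 = 0.47

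The loss is small at the low end of the assumed range and material at the high end, where the result would also describe a narrower group. FOIS, MASA and EAT-10 would remain scheduled for all residents.

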**Exclusion criteria**

1. Circumstances that interfere with the participant’s or guardian’s ability to give informed consent, for example, diminished understanding or comprehension, or a language other than English spoken.

2. Those who are on an end of life/palliative care pathway

3.Conditions that interfere with a patient's ability to comply with all treatment(s)/procedure(s) or follow study guidelines (such as behavioural issues as a result of Dementia)

4. Identified Temporomandibular Dysfunction

5. Those who are identified by the visiting oral health professional to have tooth mobility

Care staff (inclusive of nursing and allied health):

**Inclusion criteria**

1. Care staff at Maroba Aged Care

2. Care staff approved by Maroba Aged Care to participate in the study

**Exclusion criteria**

1. Staff without nursing or allied health trained qualification

# STUDY OUTCOMES

1. **Quantitative**
2. **Primary Outcome**

Feasibility and acceptability of treatment intervention. This will include the number of participants approached versus consented, completed treatment rates, and adherence to the intervention (monitored by care staff with supervision of the intervention, and completion of daily intervention sheets).

1. **Secondary Outcome(s)**

Secondary outcome measures will be collected both pre and post intervention, and are outlined in Table 1.

**Table 1** Secondary outcome measures for collection pre and post intervention

| Outcome Measure | Reference | Outcome | Description |
| --- | --- | --- | --- |
| Oral Health Assessment Tool (OHAT) | [6] | Oral health | Reliable and valid screening tool for use in aged care and with cognitive impairment; Approximately 7-8 minutes to administer; 8 items, Rating scale – 0 = healthy, 1 = changes, 2 = unhealthy; Total score out of 16, The higher the score the worse the oral health; Items that score 1 indicate intervention is required, and items scoring 2 indicate referral to a dental professional is required |
| Timed Water Swallow Test (WST) | [18] | Aspiration risk | Swallow speed is a sensitive indicator for identifying patients at risk of swallow dysfunction; Choking in 100ml WST may be a potential indicator for follow up aspiration; Measures swallow time, number of swallows and observes for signs of choking; Abnormal swallow is defined as a speed below 10ml/s (amount of water divided by elapsed time); Count the number of swallows taken to consume 100mls water; Time taken to consume 100mls water |
| Test of Mastication and Swallowing Solids (TOMASS) | [17] | Mastication ability | Quantitative assessment of solid bolus ingestion; Sensitive in detecting changes in performance ability of mastication; High interrater and test-retest reliability; Count number of bites, number of masticatory cycles per bite, number of swallows per bite; More likely to identify patients with subtle oral phase impairment or bolus transition issues; Normative ranges in older adults: number of bites (male 1.47/female 1.87), time in seconds (male 32.61/female 41.85), total number of swallows (male 3.61/female 3.5), masticatory cycle (male 37.6/female 41.65) |
| Mann Assessment of Swallowing Ability (MASA) | [24] | Identify swallowing disorders | Screening bedside tool to identify eating and swallow disorders in stroke and other diseases; Used to quantify aspiration risk; 24 clinical items; 4 components of the assessment include, general patient examination, oral preparation, oral phase, and the pharyngeal phase; 5-10 point rating scale; score out of /200, >178 = normal, 168-177 = mild, 139-167 = moderate, <138 = severe; risk of aspiration is defined on a sum of the 4 scores/categories, >170 = normal, 149-169 = mild, 141-148 = moderate, <140 = severe |
| Functional Oral Intake Scale (FOIS) | [8] | Functionality | 7 point ordinal scale; Functional level of oral intake of food and liquid; Interrater reliability high and sensitive to changes; Levels 1-3 relate to non-oral feeding; Levels 4-7 relate to varying degrees of oral feeding; All levels focus on what is/not consumed orally |
| Eating Assessment Tool (EAT-10) | [4] | Self-perceived symptoms | Screen self-perceived oropharyngeal dysphagia symptoms; Scores range from 0-40; Scores >3 are indicative of dysphagia; 10 questions rated on a 5 point scale, 0 = no problem, 4 = severe problem; Scores >15 indicative of aspiration risk; An elevated EAT-10 score indicates a higher self-perception of dysphagia |
| Mini Mental State Examination (MMSE) | [26] | Cognitive function | Widely used screening test of mental function; Evaluates cognitive impairment in older adults; 10 minutes to complete; normal = 30-25, mild = 24-21, moderate = 21-10, severe = 9-0 |

1. **Qualitative**
2. Administer Care Staff Acceptability Questionnaire to those assisting with the intervention/observing the use of the myofunctional device to rate the ease of use and cleaning of the device, the impact on workload, and perceived acceptance by residents.

Administer a Resident Acceptability Survey to all enrolled residents, regarding ease of use, comfort with use, and if there were perceived changes to oral health or swallowing following the use of the device. Assistance in reading the survey to those residents with visual impairment, aphasia, and cognitive and intellectual impairment will be provided by the care staff.

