| Infection control | Infection control procedures are outlined in the treatment manual and are consistent with Covid 19 safety and cleaning measures. Staff will be trained in cleaning protocols for the device (which are not aerosol generated) to reduce the risk of infection. Daily cleaning will be tracked with the completion of a daily check list by care staff at the ACF. |

The risks to the participants undertaking intervention is considered negligible to low risk. There is low foreseeable risk of harm or discomfort, and any foreseeable risk is no more than an inconvenience (National Statement on Ethical Conduct in Human Research, 2007).

There are no known risks for the care staff assisting with the intervention outside of usual oral care assistance.

Further considerations have been made below not specifically to risk, but rather in regard to storage and labelling, which may impact on infection control for the use of the device.

Device considerations and storage

| Potential Concern | Strategy |
| --- | --- |
| Device labelling/identification | Devices will be stored as per dentures in storage container specifically for the MyoMunchee, labelled with the participants identification number.  The MyoMunchee will be stored as per Maroba Aged Care protocol for storage and identification of usual oral hygiene products |
| Lost/misplaced device | In the event of the MyoMunchee being misplaced/lost a new replacement device will be provided |

1. **Data monitoring for safety**

Data monitoring will occur throughout the study for the safety of residents undergoing the intervention by way of:

- Pre and post intervention assessment
- During intervention with daily monitoring of completion of the trial intervention and completion of data sheets by care staff
- Weekly collection of data sheets to ensure no adverse events

Monitoring and reporting of adverse events (AE), serious adverse events (SAE) and unexpected events (UE) will be conducted as per Maroba Aged Care incident reporting system ‘ionMY’ (governance, risk management, compliance platform), and entered by care staff as per Maroba Aged Care incident reporting guidelines. Events will be reported to the principal investigator within 24 hours of the UE/AE/SAE and entered into the University of Newcastle adverse events form in Research Information Management System within 72 hours of being reported as per NHMRC (2016) guidelines.

All UE/AE/SAE will be:

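### No visible step passes flagged baseline OHAT items to the treating team or logs oral care between the two OHATs, yet single-arm pre-post oral health is to determine efficacy

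*Protocol*

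**What the plan says.** Under STUDY OUTCOMES, Table 1 describes the OHAT as eight items scored 0 to 2, with a total out of 16 and higher scores worse. It adds: "Items that score 1 indicate intervention is required, and items scoring 2 indicate referral to a dental professional is required". The OHAT is taken before and after the intervention and is the only oral-health measure in the table.

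STUDY PROCEDURES (Residents) says that at baseline "outcome measures will be collected and stored by the principal investigator from the University of Newcastle". Usual oral care and swallowing treatment are not to be altered "unless this is deemed appropriate by the usual treating speech pathologist/s at Maroba Aged Care, or the treating medical/nursing team". Device use "will commence within two weeks post pre-treatment outcome measure collection" and lasts five weeks. The recruitment text tells residents that their usual oral care is the same whether or not they take part, and the risk table relies on usual oral care continuing.

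The safety-monitoring list includes "Pre and post intervention assessment" but attaches no action to OHAT scores. For other events the protocol does name an action: "If coughing occurs through use of the device and increased saliva production, a referral will be made for speech pathology at Maroba". Reported oral discomfort also leads to a review.

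On design, "No randomisation of participants will occur", and all consented residents receive the device. The Abstract bases efficacy on pre-post assessment that includes oral health. The aim, the methodology section and OUTCOMES AND SIGNIFICANCE also speak of efficacy, and the last says the results will guide a randomised trial.

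**The concern.** The instrument's own scoring, as the protocol describes it, turns a baseline assessment into a list of residents who need oral care or a dentist. A reader of the available text cannot tell whether anyone at the facility will be told. That is a gap in resident care whatever the analysis does.

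The statistical problem sits beside it. Oral care may legitimately change between the two OHATs, no comparator shows how much change would occur without the device, and no described data field records new oral or dental care. An OHAT gain from a dental visit or improved mouth care would enter the paired comparison as though it came from the device. If such care is not recorded as it happens, a later analysis plan may be unable to recover it. At stake is how the only oral-health result is read when the randomised trial is designed.

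**Working it through.** **Is there an action on flagged items?** Table 1 describes the tool and is not a study step. The procedures have baseline measures collected and stored. The safety section lists the assessments without an OHAT trigger. The oral health professional appears only in the eligibility criteria, to identify tooth mobility. Coughing and discomfort have stated responses; flagged OHAT items have none in the visible text.

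**Is interim care recorded?**
- Daily checklists: the methodology section gives their purpose as "Treatment adherence (which will be monitored on the daily check list provided by care staff, see Appendix C, D, E, F, G". The safety section adds device cleaning.
- Medical-file form: existing data such as diagnoses, dentition, diet and independence in oral care. It has no field for dental visits or treatment during the study.
- Regression in DATA ANALYSIS: age, cognition, adherence, comorbidities and independent use of the device. It has no term for concurrent care.

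**Interval.** Up to 2 weeks before the start + 5 weeks of use = about 7 weeks, plus any wait for the post-test.

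**Illustration of size.** The protocol gives no figure to reproduce: the target of up to 50 residents comes from the available pool, and no OHAT SD, share of flagged residents or rate of interim care is stated. From the documents I take n=50 (the recruitment ceiling), the paired t-test and the 0.05 level. I assume a two-sided test, no device effect, a share p of residents gaining g OHAT points from interim care, and a background SD of change s.

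- Mean change = p·g
- Total SD = √(s² + g²·p·(1−p))
- Noncentrality = p·g·√n / total SD, referred to the noncentral t with n−1 degrees of freedom

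For p=0.25, g=2, s=1.5, n=50: mean = 0.5; total SD = √(2.25 + 0.75) = 1.732; noncentrality = 0.5 × 7.071 / 1.732 = 2.041; chance of p<0.05 = 0.516.

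Chance of a significant OHAT change with no device effect, n=50:

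| Share p, gain g | s=1.5 | s=2 | s=3 |
| --- | --- | --- | --- |
| 25%, 2 points | 0.516 | 0.356 | 0.199 |
| 25%, 1 point | 0.199 | 0.135 | 0.088 |
| 10%, 2 points | 0.138 | 0.102 | 0.074 |

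If only 30 residents contribute data (also an assumption), the first row becomes 0.333, 0.229 and 0.136. Over the n=50 table the range is about 7% to 52%, against a nominal 5%. Regression to the mean and staff attention are not in this calculation.

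**The case against.** The strongest case against has five parts.

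1. **Usual care is the default.** The recruitment text, the procedures and the risk table all keep oral care as it was, and the change clause is a clinical exception. The site also has a visiting oral health professional. This stands: a reader might infer that oral care is expected to shift widely, or that residents are cut off from dental care, and the protocol supports neither. What remains is that the exception is open and no record of its use is described.

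2. **Absence is judged on incomplete papers.** Appendices C to G (checklists), Appendix H (the OHAT form) and the treatment manual are not shown, and any of them could hold a referral prompt or care log. This also stands. The point is limited to the visible text, and a reader should not conclude that no such step exists anywhere.

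3. **If nobody acts on the scores, the OHAT itself triggers no new care.** That is fair, and it leaves ordinary changes in care plus the general weakness of any single-arm comparison. But the protocol does not state that weakness where it claims efficacy.

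4. **The hand-over may add concurrent care, and a log does not restore attribution.** Both are true. Residents' care justifies the hand-over, the log makes the added care visible, and only the wording change deals with attribution.

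5. **The consequence is limited.** The OHAT is one of seven secondary measures, the primary outcome is feasibility, and the randomised trial would settle attribution. This caps the weight of the point but does not remove it.

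**Conclusion.** The point holds for the visible protocol, with medium confidence. Flagged baseline items have no stated hand-over, interim oral care may change over about seven weeks without a described record, and the uncontrolled OHAT change is labelled efficacy. Any change from other care, regression to the mean or staff attention would then be read as a device effect.

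The size is unknown. The 7% to 52% range rests on an assumed share, gain and SD at the recruitment ceiling. A reader might take the upper end as the expected false-positive rate, but it needs a quarter of residents to gain 2 of 16 points together with the smallest SD considered, and nothing in the documents shows that interim care is that common. Where it is rare, the effect is small. The primary feasibility outcome is unaffected.

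The change is worth making because the resident-care gap does not depend on the size of the bias and the remedy is cheap.

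**What to change.** 1. **Hand-over.** State in STUDY PROCEDURES that baseline OHAT items scored 1 or 2 are passed to the treating team or the visiting oral health professional. If Appendix H or the treatment manual already says so, refer to it there.
2. **Log.** Add one field for new oral or dental care (date, type) between the two OHATs. Report its frequency alongside the OHAT change. Any result excluding residents with new care should be descriptive only, because that subset is likely to differ in baseline severity.
3. **Wording.** In the Abstract, the aim, the outcome-measures paragraph of STUDY DESIGN/METHODOLOGY, and OUTCOMES AND SIGNIFICANCE, describe the pre-post results as uncontrolled preliminary change rather than efficacy.

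The cost is one hand-over step, slight extra data entry and a few sentences. No arm, visit or resident is added. Acting on the scores may increase concurrent care, which the log would show.
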